#### ***Initial Data Inspection:***

Data will be analyzed to evaluate assumptions to inform the most valid statistical analysis. Data distributions will be assessed so that appropriate transformations may be applied where indicated and to check for outliers. Data will be examined for completeness to identify any possible systematic bias with respect to group and in particular, attrition. Analyses will be conducted using SAS v9.4. Analysis details for each hypothesis are given below.

#### **Analyses of primary outcomes:**

Buprenorphine prescribing outcomes.

We will apply a generalized linear mixed model (GLMM). The GLMM will include subject ID as a random effect and clinic as a fixed effect; the appropriate link function will be used, invoking generalized estimating equations (GEE) to account for the longitudinal (repeated measures) aspect of the data. Using GEE accounts for the repeated-measures design and uses all available data, including participants who may have missed time points and accounts for the correlation between repeated outcome measures at two time points (at 3 and 6 months). We will specify a Gaussian error distribution and identity link to compare the means of each feasibility outcome between the two arms. The primary model will estimate effects across all time points; a secondary model will include an interaction term with time to estimate effects at 3 and 6 months separately.

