Aim 2: Develop a narrative-based stigma reduction intervention and tailor it to the rural primary care setting using HCP feedback.

Aim 3: Assess the feasibility and acceptability of a stigma-reduction intervention in a pilot study in a diverse group of rural primary care HCPs.

To adapt existing interventions, we will disseminate a focused survey to 300 rural primary care physicians in Ohio, assessing key features of stigma and the relationship to buprenorphine attitudes and use. Prior to screening, we will also pre-test all survey items with 25 health care professionals with similar characteristics to our target population. The pilot will assess survey length, and check response distribution, item comprehension, and data collection procedures.

To assess intervention components, we will provide the intervention to 15 rural health care professionals and conduct a structured focus group to explore each module, assess perceptions of the intervention, identify the most salient features, and isolate barriers of concern to inform the development of a booster module.

To understand perceptions of each component in greater depth, we will conduct in-depth interviews with 15 rural health care professionals who have received the intervention.

Following completion of the booster module, we will provide the intervention to 15 rural additional health care professionals and conduct a structured focus group to assess perceptions of the booster module, identify needed changes to each module in the overall intervention, and finalize the intervention for feasibility testing.

Screening, enrollment, randomization and assessments. We will enroll 400 HCPs across 6 rural FQHCs who (1) currently practice in Ohio and (2) are eligible buprenorphine prescribers under federal law (3) do not currently prescribe buprenorphine at full capacity. Primary care providers will include physicians with board certification in internal or family medicine as well as family nurse practitioners. Because our primary outcomes are intervention feasibility, clinics will be cluster randomized into a group of 4 (intervention arm, n=267) and 2 (control arm, n=133) to increase the amount of pilot data on the intervention. We will recruit practices from Federally Qualified Health Centers (FQHCs) and FQHC look-alikes in rural, Ohio counties affiliated with OACHC. All eligible participants in enrolled practices will be screened for eligibility and asked to complete the study.

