## **Statistical Methods**

### ***Quantitative data analyses***

All tests will be based on a nominal 5% two-sided type I error probability. Confidence intervals will have nominal 95% coverage. All primary analyses will compare arms by measures of feasibility.

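### The primary model fits clinic, the randomised unit, as a fixed effect, so the arm main effect is not identified and between-clinic variance never enters its standard error

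*Combined protocol and SAP*

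**What the plan says.** Section 4.1.a sets the design: "We will enroll 400 HCPs across 6 rural FQHCs", and "clinics will be cluster randomized into a group of 4 (intervention arm, n=267) and 2 (control arm, n=133". The clinic is therefore the unit of randomisation.

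Under Analyses of primary outcomes the plan gives its only model: "The GLMM will include subject ID as a random effect and clinic as a fixed effect", "invoking generalized estimating equations (GEE) to account for the longitudinal (repeated measures) aspect of the data". The GEE is said to be a method that "accounts for the correlation between repeated outcome measures at two time points (at 3 and 6 months". The purpose is "to compare the means of each feasibility outcome between the two arms", with Gaussian errors and an identity link. On time the plan says: "The primary model will estimate effects across all time points; a secondary model will include an interaction term with time".

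Analyses of secondary outcomes reuses this approach. Quantitative data analyses adds: "All tests will be based on a nominal 5% two-sided type I error probability", with 95% confidence intervals. Section 4.3 does recognise clustering. It bases the sample size on a differences-in-differences cluster randomised design and claims 80% power for d = 1.01 with 6 clinics, but it states no ICC. No section provides a random clinic effect, a clinic-level working correlation or a small-sample correction.

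**The concern.** In a cluster randomised trial the arm comparison is a comparison between clinics, and its uncertainty comes mainly from how much clinics differ. A fixed effect for every clinic uses up all the between-clinic information, including the arm contrast itself. What remains is within-clinic information, where arm does not vary.

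Two things are at stake. The plan commits to two-sided 5% tests and 95% intervals between arms, and the model as written cannot supply valid ones. The Outcome Measures table also says that adoption will supply preliminary effect sizes for a follow-up cluster randomised trial. That trial needs the between-clinic variance, and a fixed-clinic model does not estimate it.

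**Working it through.** **Inputs from the plan.** 400 professionals in 6 clinics, split 4:2 (4.1.a). Retention 90% at 6 months, two-sided alpha 0.05, 80% power, d = 1.01 (4.3 and Statistical Methods). Analysed: 400 × 0.9 = 360, or 60 per clinic, 240 v 120 by arm.

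**Assumptions, not in the plan.** Equal clinic sizes, ICC from 0.01 to 0.20, and a within-subject correlation of 0.6 between 3 and 6 months.

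**1. The plan's own figure.** Without clustering, the detectable d is (1.960 + 0.842) × √(1/240 + 1/120) = 2.802 × √0.0125 = 0.31. The stated 1.01 must therefore include a clustering penalty. Setting 2.802 × √(0.0125 × DE) = 1.01 gives a design effect DE = 10.4. Since DE = 1 + 59 × ICC, the implied ICC is 9.4/59 = 0.16. With a t reference on 4 df, DE is 5.8 and the ICC about 0.08. So 1.01 is attainable but cannot be confirmed without the ICC.

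**2. Identification.** Intercept, 5 clinic indicators and arm make 7 columns of rank 6. The rank is also 6 without arm. Arm is the sum of the four intervention-clinic indicators, so its main effect is not identified. Software will drop a term, and the coefficient it prints depends on the coding. With time and arm × time added there are 9 columns of rank 8. Arm is still not estimable, but arm × time is. With only 3 and 6 months in the model, that term is the difference between the two effects and not the effect at either time.

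**3. Type I error if the model is repaired informally.** Dropping clinic and treating 360 professionals as independent, with one measurement each, gives error = 2 × [1 − Φ(1.96/√(1 + 59 × ICC))].

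With two measurements averaged, the variance within a clinic is (1 − ICC) × (0.6 + 0.4/2) = 0.8 × (1 − ICC), and the clinic variance is unchanged. A forced contrast of clinic means then understates its variance by the factor R = 1 + 60 × ICC/[0.8 × (1 − ICC)], and the error is 2 × [1 − Φ(1.96/√R)]. At ICC 0.05, R = 1 + 3/0.76 = 4.95, 1.96/2.224 = 0.881, and the error is 38%.

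| Assumed ICC | One measurement, clinic dropped (formula) | Two measurements, forced contrast (formula) | Simulation: both workarounds |
|---|---|---|---|
| 0.01 | 12% | 14% | about 14% |
| 0.05 | 32% | 38% | 37–38% |
| 0.08 | 41% | 47% | 46–48% |
| 0.16 | 54% | 62% | 59–62% |

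In the simulation column the lower end is clinic dropped and the upper end is the forced contrast.

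**4. Other analyses, same simulation.** GEE clustered on clinic, with ordinary robust standard errors and a normal reference, gave about 23% at every ICC. A t test on clinic means with 6 − 2 = 4 df gave about 5% at every ICC.

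**5. Power of the valid analysis at d = 1.01.** The standard error is √[(1 + 59 × ICC) × 0.0125], with a noncentral t on 4 df. Power is about 92% at ICC 0.05, 73% at 0.10 and 48% at 0.20.

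**The case against.** The strongest defence is the differences-in-differences design named in section 4.3. Baseline is collected. If it were an outcome row and the target were arm × time, the change contrast would be estimable beside fixed clinic effects. The analysis section does not say this. It names two time points, both after baseline, and places the time interaction only in the secondary model. Even with baseline rows added, clinic-by-time variation would be unmodelled, so the change contrast would have the same kind of standard-error problem.

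A reader might infer that no arm estimate can be computed at all. That goes too far. If clinic is coded as nested within arm, an equally weighted contrast of clinic means can be computed. What fails is its inference, as step 3 shows. A reader might also infer that the plan ignores clinic. It does not: the fixed effects absorb differences in clinic means. They do not carry the variance between clinics into the arm standard error.

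Finally, this is a pilot about feasibility, and the 4:2 split was chosen to gather more data on the intervention. That lowers the consequences of a wrong test. It does not remove the point, because the plan commits to 5% tests between arms and to effect sizes for the next trial.

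**Conclusion.** The point holds and should be fixed before analysis. That the arm main effect is not identified follows from the design and needs no ICC assumption. The size of the error after a workaround does depend on assumptions: 60 per clinic, a within-subject correlation of 0.6 and an unstated ICC. Over ICC 0.01 to 0.16 it runs from about 14% to about 60% against a nominal 5%, and even the one-measurement formula gives 12% at ICC 0.01. The direction does not depend on these choices as long as clinics differ at all.

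A reader might also conclude that d = 1.01 is wrong. The documents do not support that. The figure fits an ICC of about 0.08 or 0.16, depending on the reference distribution, and the plan does not say which it used.

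**What to change.** Replace the model under Analyses of primary outcomes, and with it the approach carried to the secondary outcomes:

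- **Main comparison.** A two-stage analysis of clinic means, with a t test and 95% interval on 4 df. The alternative is a mixed model with a random clinic intercept, professional nested in clinic where there are repeated measures, and arm tested on 4 between-clinic df. The clinic-level form should lead, because it is the one shown above to hold its error rate.
- **Baseline.** Adjust only where the outcome is measured at baseline, such as prescribing, knowledge, willingness and attitudes.
- **Acceptability, feasibility and appropriateness.** These are listed at 3 months only, so use a single-time-point version with no baseline term and no 3-/6-month covariance.
- **Adoption.** Compare clinic-level proportions (yes/no) and clinic-level means (patient count) on 4 df.
- **GEE and ICC.** Delete the GEE wording, and report the estimated ICC with its confidence interval.

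An unrestricted randomisation test is no substitute at the 5% level. A 4:2 split of 6 clinics has 15 allocations, so its p-value cannot fall below 1/15 = 0.067.

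**Cost.** Design, recruitment and data collection do not change. Confidence intervals will widen to the precision that six clinics can give. Section 4.3 must also change: it should state the ICC behind d = 1.01, or restate the detectable difference on 4 df.

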Enrolled participants will be evaluated at baseline, immediately following the intervention, and at 3 and 6 months after enrollment. The baseline and follow-up questionnaires will be administered via an online survey.

Follow-up in-depth interviews will be conducted to monitor the process of change in primary and secondary outcomes over time. Over the enrollment period, we will select 10 participants in the intervention arm. We will purposively select 4 individuals who newly prescribed buprenorphine during this period, 3 individuals who were not retained in the study, and 3 individuals who did not prescribe buprenorphine at all. Interviews will be conducted by key personnel who are trained interviewers. Each interview will last approximately 60 minutes.

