#### **Expected effect size and power:**

Given that this is a pilot study that will be used to power a future R01, we do not have sufficient data about the psychometric properties of the outcome measures utilized in this study among our population of interest, including the means and standard deviations. As such, we cannot estimate the specific degree of change we can detect in terms of scale points. Thus, the sample size estimation is based on a differences-in-differences cluster randomized trial with two parallel arms and a continuous outcome variable. Alpha was set to 0.05 and power was estimated at 80%. We estimate retention to be 90% at 6 months, due to limited job turnover within community health centers enrolled in the study. Based on these assumptions, a sample of 400 provides 80% power to detect a difference of  $d = 1.01$  with participants clustered in 6 clinics. This indicates we will have sufficient power to assess a difference of one standard deviation in each of the primary outcome variables.

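### The sample size rests on a difference-in-differences design, but the primary model names no baseline value and, as written, follows up only at 3 and 6 months

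*Combined protocol and SAP*

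**What the plan says.** **Power basis.** Under Expected effect size and power, "the sample size estimation is based on a differences-in-differences cluster randomized trial with two parallel arms and a continuous outcome variable". The stated result is 80% power for d = 1.01 with 400 participants "with participants clustered in 6 clinics", assuming 90% retention at 6 months. The effect is given in SD units only, because "we cannot estimate the specific degree of change we can detect in terms of scale points". No ICC is stated, nor any correlation over time.

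**Data collected.** Section 4.1.a: "Enrolled participants will be evaluated at baseline, immediately following the intervention, and at 3 and 6 months after enrollment".

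**Allocation.** Section 4.1.a: "clinics will be cluster randomized into a group of 4 (intervention arm, n=267) and 2 (control arm, n=133").

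**Model.** Analyses of primary outcomes specifies a mixed model with a random subject effect and a fixed clinic effect. It uses GEE, which "accounts for the correlation between repeated outcome measures at two time points (at 3 and 6 months"), and compares arm means. The primary model estimates one effect over time. A secondary model adds a time interaction, whose stated purpose is to separate the 3-month effect from the 6-month effect. No baseline outcome, baseline covariate or arm-by-(baseline versus follow-up) term is named. Analyses of secondary outcomes carries the same approach to willingness, knowledge and attitudes.

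**The concern.** A difference-in-differences contrast compares change from baseline between arms. The model described compares levels after randomisation. These are different estimators with different variances, so the stated detectable difference does not describe the planned analysis.

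With six randomised clinics split 4 to 2, sizeable baseline differences between arms can arise by chance. Eligible professionals may already prescribe below full capacity, so clinics can start with different patient numbers. They can also differ at the start in knowledge, willingness and attitudes. A follow-up-only comparison carries whatever part of that difference persists into the estimate. The outcome table says that the adoption measure is to supply preliminary effect sizes for the next cluster trial, so a chance imbalance could pass into that trial's planning.

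**Working it through.** **Inputs from the plan.** 400 participants; 6 clinics, 4 against 2; 90% retention, so 0.9 × 400 = 360 analysed and 360/6 = 60 per clinic (equal clinic sizes assumed); two-sided alpha 0.05; 80% power; d = 1.01.

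**Inputs not in the plan, assumed.** The ICC; the correlation c of a clinic's true mean between baseline and follow-up; the within-person correlation s.

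**1. The plan's own figure.**
- Without clustering, d = (1.960 + 0.842) × √(1/267 + 1/133) = 2.802 × 0.106 = 0.30, or 0.31 with 240 and 120 analysed. Some allowance for clustering therefore lies behind 1.01.
- Follow-up-only variance in SD units is (1/4 + 1/2) × [ICC + (1 − ICC)/60]. Solving for d = 1.01 gives ICC 0.16 with normal quantiles (multiplier 2.80), or 0.08 with a noncentral t on 4 df (multiplier 3.76).
- Difference-in-differences variance is (1/4 + 1/2) × 2 × [ICC(1 − c) + (1 − ICC)(1 − s)/60]. The same d then needs ICC 0.07–0.08 (normal) or 0.03–0.04 (t) if c = 0; about 0.16 or 0.08 if c = s = 0.5; and 0.38–0.42 or 0.17–0.22 if c = 0.8.

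So 1.01 can be neither reproduced nor refuted, and it implies different assumptions under the two designs.

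**2. Chance baseline difference between arms.** SD = √{0.75 × [ICC + (1 − ICC)/60]}:
- ICC 0.05: √(0.75 × 0.0658) = 0.22
- ICC 0.08: √(0.75 × 0.0953) = 0.27
- ICC 0.16: √(0.75 × 0.1740) = 0.36

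**3. Direction of any power difference.** Detectable d at 80% power, with ICC 0.10, 60 per clinic and a noncentral t. Baseline adjustment multiplies the follow-up-only variance by 1 − r², where r is the correlation of clinic means: r = [c·ICC + s(1 − ICC)/60] / [ICC + (1 − ICC)/60]. It is given 3 df (multiplier 4.26); the other two have 4 df.

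| c, s | Follow-up only | Difference-in-differences | Baseline-adjusted |
|---|---|---|---|
| 0, 0 | 1.10 | 1.56 | 1.25 (r = 0) |
| 0.5, 0.5 | 1.10 | 1.10 | 1.08 (r = 0.50) |
| 0.8, 0.5 | 1.10 | 0.76 | 0.81 (r = 0.76) |

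Difference-in-differences is worse than, equal to or better than follow-up only, depending on correlations that the plan does not give. Baseline adjustment never has the larger variance of the three, but it pays one degree of freedom.

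**4. The clinic term.** On follow-up data, an intercept, 5 clinic indicators, arm and time make 8 columns of rank 7, because arm is the sum of its clinics' indicators. The arm effect is not estimable. Adding a baseline covariate gives 9 columns of rank 8, so the aliasing remains. With baseline rows, clinic, time and arm-by-time together have full rank (8 of 8).

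**The case against.** **The text may include baseline.** The primary model is said to cover every time point, and section 4.1.a lists baseline as an assessment. Clinic fixed effects would also fit a difference-in-differences with baseline rows. The wording is not airtight, but the model text counts two time points and names them. Moreover, if baseline were an outcome row, a primary model without a time interaction would average a pre-intervention difference into the arm effect. Neither reading gives a difference-in-differences.

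**Randomisation already protects the comparison.** This stands. A reader might infer that the analysis targets a different quantity from the one powered, or is biased. Under randomisation both contrasts have the same expected value; only variance and chance imbalance differ.

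**Loss of power is not shown.** This stands too. A reader might infer that a precision gain built into the sample size is being thrown away. The plan gives no ICC or correlations, so no such gain can be identified.

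**Several outcomes have no usable baseline.** Also correct. Acceptability, feasibility and appropriateness rate the intervention itself, and yes/no adoption already records change from the starting position. For these, the power basis is what does not fit.

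**This is a pilot.** Feasibility is the main aim, which limits the consequences. It does not explain why the power section and the model describe different analyses.

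**Conclusion.** The mismatch holds. The sample size is justified by a change-from-baseline design, and the model names only follow-up outcomes although baseline is collected. It bears on the number of patients receiving buprenorphine and on the knowledge, willingness and attitude scales.

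The chance baseline difference left unaddressed has an SD of about 0.22 to 0.36 SD units, against a detectable difference of 1.01. That range assumes ICCs of 0.05 to 0.16 and 60 people per clinic. How much of it reaches the follow-up contrast depends on how far clinic differences persist.

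The imbalance enters the arm contrast in this way only once clinic is dropped or made random. With the clinic fixed effect as written, the arm effect on follow-up data cannot be estimated at all. The baseline term and the clinic term must therefore be settled together.

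**What to change.** 1. **Patient count, knowledge, willingness and attitudes:** add the outcome's baseline value as a covariate, or include baseline as an outcome row with an arm-by-time contrast. Name that arm difference as the primary result for the outcome.
2. **Clinic term:** replace the clinic fixed effect by a clinic random effect with small-sample degrees of freedom. A baseline covariate alone does not make the arm effect estimable.
3. **Acceptability, feasibility, appropriateness and yes/no adoption:** do not base their power on a difference-in-differences; state a basis suited to each.
4. **Power section:** state the ICC and correlations behind d = 1.01, and restate the detectable difference for the model actually used.

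The change is to the wording of the analysis and power sections, plus a fresh power calculation. Baseline assessments are already scheduled. The price is about one of the few cluster-level degrees of freedom, and the restated detectable difference may be less favourable than 1.01.

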| Primary | Feasibility     | 3 months   | 
Feasibility refers to the ease in which a new intervention can be used within a specific setting. It will be measured using the 4-item FIM. We will also measure feasibility through interviews with health care professional participants to understand barriers and facilitators of implementing the intervention in the rural primary care setting.
                                                                                                                                                                                                                                                                                                                          |
|         | Appropriateness | 3 months   | 
Appropriateness refers to the perceived alignment of the intervention within a particular practice setting and will be measured by the 4-item Intervention Appropriateness Measure (IAM). We will also measure appropriateness in in-depth interviews with health care professionals, exploring the most salient features of the intervention and its fit with current training needs.
                                                                                                                                                                                                                                                                                          |
| Primary | Adoption        | 6 months   | 
Adoption refers to intentions or actions to adopt an EBI. We will measure adoption as whether a HCP initiates buprenorphine prescribing for the first time or increases their patient panel (yes/no) and as the total number of patients receiving buprenorphine for each HCP. This measure will also allow us to measure preliminary effect sizes related to buprenorphine prescribing which are critical for the
                                                                                                                                                                                                                                                              |

|           |                                            |          |                                                                                                                                                                   |

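### Adoption is declared at 6 months, but the primary model pools 3 and 6 months and leaves the 6-month effect to a secondary model

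*Combined protocol and SAP*

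**What the plan says.** The Outcome Measures table in Section 4.1 gives each outcome a time frame. Adoption is a primary outcome and its row reads "Adoption | 6 months". Its definition begins "We will measure adoption as whether a HCP initiates buprenorphine prescribing for the first time or increases their patient panel (yes/no" and adds the number of patients on buprenorphine per professional. The same row states a purpose: "This measure will also allow us to measure preliminary effect sizes related to buprenorphine prescribing", for use in a follow-up cluster randomized trial. All four secondary outcomes are listed at 6 months. Acceptability, feasibility and appropriateness are listed at 3 months.

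Under Statistical Methods, Analyses of primary outcomes, the subheading is buprenorphine prescribing. The method is said to use all available data and "accounts for the correlation between repeated outcome measures at two time points (at 3 and 6 months"). The estimate is then assigned: "The primary model will estimate effects across all time points; a secondary model will include an interaction term with time", and only that secondary model gives a separate effect for each visit. Clinic enters this model as a fixed effect. Analyses of secondary outcomes carries the same approach over to those outcomes. No section names the 6-month contrast as the primary estimate for any outcome.

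**The concern.** The outcome table and the analysis section define different primary quantities for the same outcome. A model without an arm-by-time term returns one arm effect, roughly the average of the effects at the two visits. A reader who takes the outcome table at its word would expect the arm difference at 6 months, and that figure appears only as a secondary result.

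The assumption that would reconcile the two is a constant effect, which the plan neither states nor justifies. The design gives some reason to doubt it. Section 4.1.c schedules a booster on prescribing barriers at one month, further training and waiver receipt are followed to 6 months, and adoption means a first prescription or a larger panel. A delayed effect is plausible, although not established.

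At stake is which number the trial reports as its adoption effect. Two candidate effects will exist for an outcome meant to inform the next trial, and the plan gives primary status to the one that does not match its own time frame.

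**Working it through.** **Inputs from the documents.** Adoption is primary at 6 months (Outcome Measures). The model uses outcomes at 3 and 6 months with Gaussian errors and an identity link, so effects are mean differences and average additively (Analyses of primary outcomes). Six clinics are randomized 4 to 2, with 267 and 133 participants (Section 4.1.a). Alpha is 0.05, power 80%, retention 90%, detectable d = 1.01 (Section 4.3). Tests are two-sided (Quantitative data analyses).

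**Assumed, because the documents give no values.** r = 3-month effect / 6-month effect; ρ = within-person correlation between the two visits; equal weight and equal variance at both visits.

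**1. The plan's own figure.** d = (1.960 + 0.842) × √[DE × (1/n1 + 1/n2)], with DE = 1 + (m − 1) × ICC. At 90% retention n1 = 240.3, n2 = 119.7 and m = 360/6 = 60. With no clustering d = 0.31. No ICC is stated, so 1.01 can be neither reproduced nor refuted. It requires DE ≈ (1.01/0.313)² ≈ 10.4, an ICC of about 9.4/59 ≈ 0.16. With a t reference on 4 degrees of freedom the implied ICC is about 0.08. Both are plausible. Section 4.3 does not say whether d refers to the pooled or the 6-month effect.

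**2. What the primary model estimates.** Pooled effect = (3-month + 6-month)/2 = 6-month effect × (1 + r)/2.

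| r | pooled / 6-month effect | pooled d if 6-month d = 1.01 |
|---|---|---|
| 0 | 50% | 0.51 |
| 0.25 | 62.5% | 0.63 |
| 0.5 | 75% | 0.76 |
| 0.75 | 87.5% | 0.88 |
| 1 | 100% | 1.01 |

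If the effect wanes, r exceeds 1 and the pooled value is too large. At r = 1.5, for example, it is (1 + 1.5)/2 = 125%.

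**3. What pooling buys.** Pooled SE / single-visit SE = √[(1 + ρ)/2], which is 0.81, 0.87, 0.92 and 0.95 for ρ = 0.3, 0.5, 0.7 and 0.8. This is the participant-level ratio; the gain is smaller where stable clinic differences dominate the variance.

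Scale the 6-month contrast to 80% power. Power of the pooled test is then Φ(2.802 × [(1 + r)/2] / √[(1 + ρ)/2] − 1.960).
- r = 1: 93.5% at ρ = 0.3, falling to 82.0% at ρ = 0.9.
- r = 0.5: 74.1% at ρ = 0.3, falling to 57.8% at ρ = 0.9.

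Pooling helps power only if (1 + r)/2 > √[(1 + ρ)/2], that is r > 2√[(1 + ρ)/2] − 1. This threshold is 0.61 at ρ = 0.3, 0.73 at ρ = 0.5 and 0.90 at ρ = 0.8.

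**4. Can the planned model supply the 6-month contrast?** Every participant in a clinic has the same arm, so the arm indicator is the sum of the four intervention-clinic indicators. With clinic as a fixed effect, arm adds no new column. Adding arm-by-time identifies the change in the arm difference between 3 and 6 months, but not the difference at 6 months. The pooled arm effect is aliased in the same way.

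**The case against.** The strongest defence is that the 6-month effect is already prespecified, in the secondary model, so only the label is in dispute. That is largely right: nothing has to be added to data collection. The label still decides which result is the headline, and the plan's own time frame points to the other one.

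Pooling can also be defended in a small pilot. At ρ = 0.5 the variance falls by 25%, and with a constant effect power rises. This stands, and it is why the pooled estimate should be kept as supportive.

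Three stronger readings are tempting, and the documents do not support them.
- A reader might infer that the headline adoption effect will be diluted. Accrual of prescribing describes the level in each arm; it does not show that the difference between arms grows. The distortion may be zero or may run the other way.
- A reader might infer that the pooled figure will be carried to the follow-up trial. The outcome table says only that the adoption measure will yield preliminary effect sizes, not which model's estimate goes forward.
- A reader might infer that acceptability, feasibility and appropriateness are pooled as well. The model text does refer to feasibility outcomes, but under a prescribing subheading, and no section says these three scales are collected at 6 months. If they exist only at 3 months, there is nothing to pool.

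**Conclusion.** The mismatch holds for adoption and, through Analyses of secondary outcomes, for the secondary outcomes listed at 6 months. It follows from the text alone and needs no assumption about the effect. Its numerical consequence does: the pooled effect is 50% to 100% of the 6-month effect for r between 0 and 1, and above 100% if the effect wanes. Those figures rest on assumed r and on equal weighting of the two visits.

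This is a question of which planned estimate is primary; no analysis is missing. It should be settled before analysis because the correction is cheap and removes the choice between two adoption effects after the data are seen. The aliasing of arm with clinic must be resolved at the same time, or neither the pooled nor the 6-month arm effect can be estimated from the model as written.

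**What to change.** - In Analyses of primary outcomes, name the arm contrast at 6 months from the arm-by-time model as the primary estimate for adoption. In Analyses of secondary outcomes, do the same for outcomes listed at 6 months. Report the 3-month and pooled effects as supportive.
- Replace the clinic fixed effect with a treatment of clinic that leaves arm estimable, for example a clinic random effect with a small-sample correction, or a clinic-level analysis of the 6-month outcomes.
- State that the acceptability, feasibility and appropriateness scales are analysed at 3 months, if they are also collected at 6 months.
- If the sponsor does want the average over both visits, say so in the outcome table and justify it.

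The visits and data stay the same. The change to the clinic term is a change of model as well as of wording, and inference from six clinics will be imprecise under any valid choice. The specific cost of giving up pooling is the precision shown above, and it falls only where the effect is constant or nearly so.
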